#### Student confidence

Student confidence will be measured prior to placement and again at the end of placement using the Student Level of Confidence Questionnaire, developed specifically for occupational therapy students to complete in relation to their clinical placement experiences [33]. The questionnaire is a self-report measure including 41 items. Students rate their confidence from 1 (strongly disagree) to 5 (strongly agree), and scores are summed for a total score ranging from 41 to 205. The questionnaire has demonstrated high internal consistency (Chronbach’s alpha = .96), and principal component analysis, with oblique rotation, demonstrated the items formed one ‘confidence’ component scale [37]. According to the designers of the instrument, there is evidence that the tool is responsive to change in confidence levels both within a placement period (6 weeks duration tested in the study) and across placements (four placement periods).

#### Placement experience

*Student* placement experiences will be assessed using survey and focus group methods after the completion of the placement. Survey data will be collected using the 7-item SPEF-R companion instrument that asks the student to rate their experience of being oriented to the placement organisation, how welcome they felt within the workgroup, whether the clinical educator’s expectations were clear, whether they felt supported and how they felt about the evaluative experience. Responses are indicated using a 5-point Likert scale ranging from 1 = *strongly disagree* to 5 = *strongly agree*. Summed responses provide scores ranging from 7 to 35. In addition, a 14-item survey designed to assess student satisfaction with placement will be completed by students of both placement types, as the questions are generic [38]. This survey also employs a 5-point Likert scale ranging from 1 = *strongly disagree* to 5 = *strongly agree*. In addition to survey data, participating students will be invited to contribute to a focus group in which their perceptions of the meaning, value and quality of their placement experiences will be explored.

*Supervisor and educator* perceptions of SCP and TCP opportunities will be assessed using an online survey developed to mimic the placement experience questions posed to students. Responses to the questions will be indicated using a 5-point Likert scale ranging from 1 = *strongly disagree* to 5 = *strongly agree*. Educators involved in the delivery of the placement experiences will also be invited to contribute to focus groups that explore their perceptions of satisfaction and quality of the placement for early years’ occupational therapy students.

### Blinding

This is a single-blinded RCT where the assessors of the examinations are blind to the group to which students were allocated. Completed examination papers will be checked centrally to ensure no notes are included on the papers that reveal student allocation to SCP or TCP; the papers will then be distributed to markers who have no other role in the study. The examination scores will be collated and entered into the database by the project manager, who is not blinded to student group but has no interaction or history with any of the participating students. The SCP and TCP supervisors and SCP content deliverers cannot be blinded to group, nor can the student participants.

### Data monitoring and management

A data monitoring subcommittee will oversee data quality. The members are the lead chief investigator, an investigator with significant statistical expertise, an investigator representing the economic analysis team, the national project manager and the national research assistant. The project manager will undertake day-to-day management of the project. Each site will have a local research team consisting primarily of a site coordinator and research assistant. The local research teams are responsible for fidelity of delivering the intervention and collecting the data on their site. They will be provided with in-person training by the project manager at their site prior to implementing the intervention; the project manager will also maintain regular contact before, during and after the intervention to ensure the efficient collection of data according to the protocol. The local research assistants will collect and submit the data to the project manager. The national research assistant will enter the data into a project database for cleaning and analysis. Missing data will be identified centrally, and the local teams will be responsible for securing it, following ethically approved processes.

#### Statistical analyses methods

All data will be entered into a purpose-designed REDCap (https://projectredcap.org/) database, cleaned and assessed for missing data. Summary statistics will be used to describe the sample. To evaluate whether students who attend an SCP achieve non-inferior outcomes to those who attend a TCP, differences in achievement on the post-placement examination score will be evaluated using analysis of covariance (ANCOVA). A mean difference of ≥7 points on the examination score between students will be considered an educationally meaningful difference. Covariates included in the analyses will include broad placement type (vocational rehabilitation, physical rehabilitation or mental health) and any demographic variables identified as important during baseline analyses. Secondary outcomes related to whether students who attend an SCP achieve non-inferior outcomes to those who attend a TCP will be assessed using odds ratios between groups in predicting overall pass/fail grades on the SPEF-R, evaluated using binary logistic regression. Independent variables included in the analyses as possible covariates will include gender, age, broad placement type and any demographic variables identified in baseline analyses as important. Differences between SCP and TCP groups in achievement of a pass/fail grade on each of the four completed sections of the SPEF-R will be assessed using chi-square tests. Scores between SCP and TCP groups for individual SPEF-R items (scored on a 5-point ordinal scale) will be compared using a Mann-Whitney *U* test. An overall difference >1 point on the 5-point scale between groups will be considered educationally important.

To evaluate whether students and clinical educators report similar professional practice learning opportunities during SCP compared to TCP, the differences in frequencies of *not applicable* and *insufficient observation* items checked in the total SPEF-R by (1) students and (2) clinical educators will be compared using an independent samples *t* test, using 95% confidence intervals of the estimated mean difference between groups to identify differences.

To evaluate whether students who experience an SCP report non-inferior levels of confidence during placement outcomes compared to those who experience a TCP, the difference between change scores on the confidence questionnaire between SCP and TCP groups will be assessed using an independent samples *t* test. Between-group analyses of mean total score differences on this questionnaire, both pre- and post-SCP and TCP, will be determined using independent samples *t* tests. Within-group differences will be established using paired samples *t* tests.

To assess students’, educators’ and supervisors’ placement experiences, data from the SPEF-R student review of professional practice placement survey, Student Evaluation of Placement questionnaire, and Clinical Educator Evaluation of Placement questionnaire will be summarised and reported descriptively. The 5-point Likert-style item responses on each questionnaire will be reported graphically. Differences in item ratings between groups of participants will be assessed using independent samples *t* tests*.* Additional thematic analyses will be carried out on written comments made on any of the instruments in conjunction with data obtained through focus group interviews. All qualitative data will be analysed inductively to address the question of perceived placement value and quality.

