### Randomisation and allocation

Using a procedure specified by the national research team, the local research assistant at each site will recruit students to the trial, collect consent forms and allocate students to either the SCP or TCP group in a 1:1 ratio. A software package will be used to generate the random allocation sequence of students who have consented to submit their data for the trial. This software is freely available from the Internet (http://random-allocation-software.software.informer.com/2.0/) and is described in the literature [34]. The allocation is performed at each site by the local research assistant utilising block randomisation once student enrolment in the unit of study is determined.

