A range of detailed case scenarios have been developed for the three settings, including realistic and comprehensive case file notes and briefing documents that describe clients who require occupational therapy services within one of the three targeted settings. Steps were taken to optimise immersion in the SCP as part of the design process. For instance, university rooms and other spaces used for SCP will be branded with a fictitious placement provider name. A mock corporate placement intranet website with no university branding has been established to host resources and information for students and the staff involved. Client-related forms and referral documents were designed to emulate what might be used by occupational therapy providers and were branded with a logo. To add to the authenticity of the SCP placement, external occupational therapy professionals practising in the relevant field will be employed to provide supervision of the SCP students and to assess students’ learning outcomes.

Implementation of the 40-hour SCP intervention is structured as follows:Students will work with practising clinical supervisors and simulation facilitators in small groups with an SCP supervisor-to-student ratio of 1 to 9 or 10.Tutorial rooms and small offices on the university campus, or off campus if such facilities are available, are allocated for the placement as working spaces for each of the simulated placement days.An induction program is provided on the first day to introduce students to the workplace, supervisor(s), placement structure and content, work processes and expected professional behaviours.Each student will work with two case scenarios in particular, one in significant depth involving a simulation patient, and they will also be exposed to a further two or more cases during the 40-hour SCPStudents will work in small groups (with an average of three students per group, ranging from two to four students) to complete a series of simulation activities pertaining to their primary case scenario involving:

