### The TCP comparison group

The TCP will match the SCP in terms of duration (40 hours over 5 days), timing (implemented at the same time or within 1 week of each other), evaluation and setting (vocational rehabilitation, mental health or community-based physical rehabilitation). Students will be placed as individuals or in pairs, according to the needs and limitations of the particular external placement provider.

The learning outcomes for the clinical placement program are the same for the SCP and TCP students and will be communicated to them and the clinical educators prior to placement. The overarching learning outcomes are that students will develop and demonstrate behaviours appropriate to the occupational therapy profession, including:Professional self-conductSelf-management skills (i.e. effective time management, assuming responsibility for own learning, demonstrating initiative and taking responsibility for own actions and responses to supervision and constructive feedback)Effective communication with co-workers and service users and ability to work as part of a teamSkills in effective client information gathering from a range of sourcesAbility to identify a client’s occupational performance issues and assess the impact of environmental and social factors on the client’s ongoing participation and engagement

A comparison of the SCP and TCP pathways is presented in Fig. 3.

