### Instruments and measures

Outcomes will be assessed using a variety of tools to gather both qualitative and quantitative data to address the research questions. Data will be collected immediately prior to or at the beginning of placement, on completion of placement and at the end of the unit of study (see Table 2). Demographic data including student age, gender, university, prior qualifications and prior placement experience will also be collected.

**Table 2 Tab2:** Description of the instruments used to collect data across the trial

Instrument	Type	Timing	Respondent
SPEF-R	Paper-based	Complete across placement week, finalising during morning of 5^th^ day of placement	Clinical supervisors
SPEF-R, self assessment	Paper-based	Complete across placement week, finalising during the 5^th^ day of placement	Students (self-report)
Pre-placement questionnaire	Paper-based	Pre-placement briefing 1 week prior to placement *Or* morning of 1^st^ day of placement	Students (self-report)
Post-placement questionnaire	Paper-based	Afternoon of 5^th^ day of placement	Students (self-report)
SPEF-R, student review	Paper-based	Complete across placement week, finalising during the afternoon of 5^th^ day of placement	Students
Examination	Paper-based	Within 4 weeks of placement conclusion	Students
Sessions evaluation	Online	Within 2 weeks of placement conclusion	SCP students only
Focus group feedback	Transcribed audio	Within 4 weeks of placement conclusion	Students Clinical educators
Clinical educator survey	Online	Within 2 weeks of placement conclusion	Clinical educators (clinical supervisors and simulation facilitators)
Cost data collection	Digital	Across the full extent of the trial	Partner university site coordinators, investigators, placement support staff and project support staff

*SPEF-R* Student Practice Evaluation Form-Revised

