#### Written examination (primary outcome)

Whether students who attend the SCP achieve non-inferior outcomes to those attending a TCP in development of professional skills will be determined according to the results of an end-of-placement examination. The written examination will be implemented 1–4 weeks after placement is completed. It will require students to use (1) reasoning skills to integrate knowledge and professional skills relevant to the broad context of the theoretical unit and placement experience (i.e. vocational rehabilitation, mental health or community rehabilitation) and (2) expected professional competencies commensurate to the students’ stage of professional development. The examination will constitute a series of questions based on a scenario-based clinical report provided at the beginning of test. The aim is to test students’ skills in gathering and integrating pertinent information about the client; their capacity to identify relevant occupational performance issues and capacities and environmental barriers to performance; and their skills in identifying further information, sources and methods that could be used to gather information relevant to the client in the scenario.

The examination will be scored using a continuous scale, ranging from 0 to 100%. The examinations will be graded by a panel of clinical educators who will be blinded to the placement type undertaken by each student. They cannot be reliably blinded to university of origin because of the distributed timing of implementation. The panel will use an examination-specific marking rubric [36] and be trained through a series of workshop sessions involving grading a number of examinations and comparing and discussing the relative results. An inter-rater reliability assessment will be employed to track the readiness of each member of the panel to grade student examinations. An ICC of at least 0.7 will indicate acceptable reliability.

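### The primary ANCOVA names no term for site, the randomisation stratum, and treats SCP students who share a supervisor as independent; only the second raises the risk of false non-inferiority

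*Protocol article*

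**What the plan says.** All references are to the protocol article.

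- **Primary model** (Statistical analyses methods). The post-placement examination score is compared by ANCOVA. The covariate sentence reads "Covariates included in the analyses will include broad placement type (vocational rehabilitation, physical rehabilitation or mental health) and any demographic variables identified as important" at baseline. Neither site nor supervisor group is named.
- **University** (Instruments and measures). It appears among the baseline variables: "Demographic data including student age, gender, university, prior qualifications and prior placement experience will also be collected". It can therefore enter the model, but only if judged important, and six universities are not eight sites.
- **Randomisation** (Randomisation and allocation). "The allocation is performed at each site by the local research assistant utilising block randomisation", in a 1:1 ratio. Location and timing gives eight sites.
- **Sample size.** 240 students are raised to 340 for clustering by site (ICC 0.007, cluster size 50 to 60) and to 425 for 20% attrition. Supervisor groups are not allowed for.
- **Teaching groups.** SCP students work in "small groups with an SCP supervisor-to-student ratio of 1 to 9 or 10" (The SCP intervention). For TCP, "Students will be placed as individuals or in pairs" (The TCP comparison group).
- **Stream** (The SCP intervention). Each site chooses its practice stream, so stream is a site-level variable.

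**The concern.** An analysis should reflect the way students were randomised and taught. Here the design has two layers that the named model leaves out.

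The first is site. Sites differ in curriculum, in timing and in whether the block replaces or adds to existing placement hours. Stream takes up only part of that variation. The sample size section pays for site clustering with 100 extra students, yet the analysis names no site term.

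The second is the supervisor group. SCP students who share a supervisor for a week may have correlated scores; TCP students have at most one partner. A model that treats all students as independent then understates the variance of the SCP mean. In a non-inferiority trial, too narrow an interval favours the conclusion being sought. That conclusion also decides whether the economic evaluation takes the cost-minimisation route.

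A third, smaller matter is that "any demographic variables identified as important during baseline analyses" comes with no criterion, so the adjusted model is not fixed in advance. The SPEF-R logistic model has a similar open-ended clause.

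**Working it through.** **Inputs from the article:** 240, 340 and 425 students; site ICC 0.007; site cluster size 50 to 60; margin 7 points; alpha 0.05 (sidedness not stated); power 0.80; SCP groups of 9 or 10; 425 sought from 774 eligible (55%); 20% attrition.

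**Assumptions:** one-sided 2.5% as the nominal rate; supervisor-group ICC 0.007 to 0.10 (none is given); TCP students independent.

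**1. The plan's own figure.** Design effect = 1 + (m − 1) × ICC. With m = 60: 1 + 59 × 0.007 = 1.413, and 240 × 1.413 = 339.1. Then 340/0.8 = 425. The stated totals reproduce at the upper end of the cluster size. The 120 per group cannot be checked because no SD is given; it corresponds to an SD of 19.35 at one-sided 2.5%.

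**2. Site left out.** Under balanced 1:1 allocation within site, true SE / model SE = √(1 − ICC). False non-inferiority at the margin = 1 − Φ(1.96 / ratio).

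| Site ICC | SE ratio | False non-inferiority |
|---|---|---|
| 0.007 (stated) | 0.9965 | 2.46% |
| 0.05 (assumed) | 0.975 | 2.2% |
| 0.10 (assumed) | 0.949 | 1.9% |
| 0.20 (assumed) | 0.894 | 1.4% |

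The rate never exceeds nominal. This formula gives stream no credit. In simulation with stream in the model, a site ICC of 0.20 gave 1.8%.

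**3. SCP supervisor groups ignored.** DE = 1 + (m − 1) × ICC in the SCP arm and 1 in the TCP arm, so true SE / model SE = √((DE + 1)/2).

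Example with m = 9.5 and ICC 0.05: DE = 1.425; ratio = √(2.425/2) = 1.101; 1 − Φ(1.96/1.101) = 3.75%.

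Fewer students per group may be analysed. If consenters and non-consenters are mixed in the groups, 9.5 × 0.55 × 0.8 ≈ 4.2 remain.

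| Group ICC (assumed) | m = 9 to 10 | m ≈ 4.2 |
|---|---|---|
| 0.007 | 2.7% | 2.6% |
| 0.02 | 3.0% | 2.7% |
| 0.05 | 3.7–3.8% | 3.0% |
| 0.10 | 4.9–5.2% | 3.4% |

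If alpha 0.05 was meant one-sided, m = 9 to 10 gives 6.7–6.9% at ICC 0.05 and 8.2–8.6% at 0.10.

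**4. Both omissions together.** Simulation used 8 sites of 44 students, blocked 1:1 within site, a true difference at the margin and 10,000 runs per setting. With 22 SCP students per site it formed two groups of 11, slightly above the planned size. With both ICCs at 0.05, false non-inferiority was 3.8% with stream only and 4.1% with site in the model. Adding site alone therefore does not cure the group problem. With about 4.4 analysed per group and an assumed site ICC of 0.20, the stream-only model gave 2.6% (group ICC 0.05) and 3.1% (0.10). Monte Carlo error is about 0.2 percentage points; the run with both ICCs at zero gave 2.8%.

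**5. Power if groups are allowed for.** With 340 analysed, SD 19.35, site ICC 0.007 and m = 9.5, power is about 0.92 at group ICC 0, 0.86 at 0.05 and 0.80 at 0.10.

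**The case against.** The strongest objection is that the harmful part rests on an assumed ICC, and that the design argues for a low one. The outcome is a written examination taken one to four weeks later, not a supervisor's rating. It is marked by a trained panel blind to arm, and SCP delivery follows manuals. At a group ICC of 0.007 the excess is trivial. Groups are also unlikely to be analysed whole, and if sites differ strongly the two omissions largely offset. All of this stands, and it limits the size of the problem. It does not change the direction, and an offset between two unknown variances is not something to rely on.

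A second objection is that partially nested models and exact covariate lists belong in a SAP, which is not shown. That is fair for the detail. But the article does name the model and its covariates, and those do not match its own randomisation and sample size sections.

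Readers might also infer more than the documents support:

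- *That omitting site raises false non-inferiority.* It does the reverse under the planned 1:1 blocks within site. The Discussion mentions a risk in procuring TCP places, but no unequal allocation is planned.
- *That recognising the university biases marking.* The article says of markers "They cannot be reliably blinded to university of origin because of the distributed timing of implementation", but they remain blind to arm, and one trained panel uses a rubric with a reliability threshold.
- *That choosing covariates at baseline distorts the standard error.* Nothing shows this; no use of outcome data in the choice is described.
- *That site is wholly excluded.* University may enter through the demographic clause.

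**Conclusion.** The point holds in a limited form, as a should-fix.

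- **Site.** The named analysis is inconsistent with the randomisation and the sample size. The cost is precision: nothing of note at the stated ICC of 0.007, more if sites differ more than that.
- **SCP supervisor groups.** Treating these students as independent is anti-conservative for any positive group ICC. Against a nominal one-sided 2.5%, the rate is about 2.7% (ICC 0.007) to 5% (ICC 0.10) if all nine or ten are analysed. It is about 3.0% to 3.4% (ICC 0.05 to 0.10) with roughly four analysed per group. The direction follows from the design; the size depends on the assumed ICC and group size.
- **Covariates.** The open list is a weakness of pre-specification and no more.

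The documents do not support a claim that all three features together make false non-inferiority more likely.

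**What to change.** - Put site in the primary model as a fixed effect with eight levels. Stream is then absorbed, since each site chooses its own.
- Account for SCP supervisor group with a random effect in a partially nested model, with TCP students or pairs as their own clusters and small-sample degrees of freedom. At the least, make this a pre-specified sensitivity analysis for the non-inferiority conclusion.
- Replace the open demographic clause, here and in the SPEF-R logistic model, with a fixed list from variables already collected: age, gender, prior qualifications and prior placement experience.

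The cost is analysis wording and one identifier for SCP supervisor group. Data collection was complete when the article was accepted, but each student's supervisor completes the SPEF-R, so the identifier should be recoverable. The change should be fixed before the arms are compared. The confidence interval widens somewhat if group clustering is present; on the figures above, power with 340 analysed stays at about 0.80 or more up to a group ICC of 0.10.

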### Aims and research questions

The study aims to explore the differences between a 40-hour block SCP experience and a 40-hour block TCP experience in terms of development of professional competencies and fieldwork confidence, and to determine the comparative delivery costs for the SCP and TCP programs as borne by the university.

The research questions are:Do students who undertake an SCP in the early years of an entry-level occupational therapy program achieve *non-inferior outcomes* in their development of professional practice skills compared with those who attend a TCP, as assessed by a post-placement written examination (primary outcome), Student Practice Evaluation Form-Revised (SPEF-R) evaluation [31, 32] and end-of-semester study unit score?Do students and supervisors report similar professional practice learning opportunities when students complete an SCP compared to those students who complete a TCP, assessed using a self-report survey, and similar frequencies of *not applicable* and *insufficient observation* items in the SPEF-R?Economic research questions: If non-inferiority is established, does SCP cost less than TCP from the perspective of (1) the health sector and (2) the universities as providers?If costs of SCP are not less than those of TCP, are there offsetting benefits which still make the SCP value for money?
Do students who experience an SCP in the early years of an entry-level occupational therapy program report self-confidence outcomes that are non-inferior to those who attend a TCP, as measured by the Student Confidence Questionnaire [33]?What are the perceptions of quality and adequacy of the TCP versus SCP experience of students and clinical educators?

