Individual student performance on each item is rated on a 5-point scale as follows: 1. *Performs unacceptably*; 2. *Experiencing difficulty or performs marginally*; 3. *Performs adequately*; 4. *Performs proficiently*; and 5. *Performs with distinction*. Scores of 1 or 2 indicate a failing performance. Students must pass all core units in each of the four domains of the SPEF-R to achieve an overall pass in the placement. Data will be collated to determine whether students pass overall, which domains are passed and the sum of the individual item scores in the SPEF-R. The frequencies of items identified as *not applicable* and *insufficient observation* in the SPEF-R will also be determined for each student. The student and supervisor reports of comparable learning experiences in each placement setting will be compared using data extracted from the SPEF-R and a self-report survey (research question 4).

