#### Unit grade

The overall grade for the unit of study will be collected for each participating student and will be reported using a continuous scale ranging from 0 to 100%. A mean difference of ≥7 points on the subject/unit grade between groups will be considered an educationally meaningful difference. This difference was selected as meaningful because it represents ≥50% of each passing grade scale (e.g. Pass = 50–65% in some universities and 50–60% in others), and a difference of 7 points is likely to result in a shift in the allocated grade for a student.

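### Non-inferiority on SPEF-R overall pass and on student confidence is asked, but the analyses named for them have no margin or confidence-limit rule

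*Protocol article*

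**What the plan says.** In the protocol article, Aims and research questions, the first question asks for non-inferior outcomes on the examination (primary), on the "Student Practice Evaluation Form-Revised (SPEF-R) evaluation [31, 32] and end-of-semester study unit score". A later question asks whether SCP students "report self-confidence outcomes that are non-inferior to those who attend a TCP". A further question is worded as similarity: "Do students and supervisors report similar professional practice learning opportunities".

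Statistical analyses methods then assigns an analysis to each:

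- **SPEF-R overall pass.** The section says that "non-inferior outcomes to those who attend a TCP will be assessed using odds ratios between groups in predicting overall pass/fail grades", using binary logistic regression. No margin or confidence-limit rule follows. The four SPEF-R domains are compared by chi-square tests.
- **Confidence.** To find out whether SCP students "report non-inferior levels of confidence during placement outcomes compared to those who experience a TCP", change scores are compared by an independent samples t test. No margin is set on the 41–205 scale.
- **Learning opportunities.** Counts of not-applicable and insufficient-observation items are compared by a t test, with 95% confidence intervals used to identify differences. No similarity bound is given.

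The only non-inferiority margin defined is 7 points on the examination score (Sample size). The unit grade has a 7-point threshold, justified because "it represents ≥50% of each passing grade scale (e.g. Pass = 50–65% in some universities and 50–60% in others".

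**The concern.** A non-inferiority claim needs a statement of how much worse is acceptable, and a rule that the confidence limit must exclude anything worse than that. An odds ratio or a t test without a margin answers a different question: whether a difference can be detected. With few failures or noisy scores, failing to detect one is the likely result even when the data leave room for a material deficit.

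This is more than detail that an article may leave to an analysis plan. The article itself ties the non-inferiority wording to named analyses and stops there. At stake are two stated secondary research questions, plus the similarity question. If the SPEF-R and confidence results come out non-significant, nothing in the document tells a reader whether non-inferiority has been shown.

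**Working it through.** **Inputs from the document (Sample size; Unit grade).** 120 per group before the clustering allowance; 340 in total after it, so 340/2 = 170 analysable per arm; 340/0.8 = 425 to recruit, which reproduces. Pass bands 50–65 and 50–60.

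**Assumptions.** The document gives no SPEF-R pass rates, no SD and no secondary margins. The pass rates, standardised deficits and 5- and 10-point margins below are illustrations. Calculations are unadjusted.

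**1. What a non-significant odds ratio leaves open.** With equal true pass rates p, SE(log OR) = √[2/(n·p(1−p))], and the expected 95% CI is exp(±1.96·SE).

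| n per arm | p | SE | Expected 95% CI for OR |
|---|---|---|---|
| 170 | 90% | √(2/15.3) = 0.362 | 0.49 to 2.03 |
| 170 | 95% | √(2/8.075) = 0.498 | 0.38 to 2.65 |
| 120 | 90% | √(2/10.8) = 0.430 | 0.43 to 2.32 |
| 120 | 95% | √(2/5.7) = 0.592 | 0.31 to 3.19 |

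Each interval includes 1, and each includes a halving of the odds of passing.

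**2. The conclusion depends on the missing margin.** At 170 per arm and 90% in both arms, the 95% CI half-width for the risk difference is 1.96·√(2·0.09/170) = 1.96·0.0325 = 6.4 percentage points. An observed difference of zero would be non-inferior against a 10-point margin and not against a 5-point one.

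**3. Error rate at the margin if non-significance were the rule.** P(non-significant) = 1 − Φ(δ/SE − 1.96).

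- SPEF-R pass, 95% v 85%, 170 per arm: SE = √[(0.0475 + 0.1275)/170] = 0.0321; 0.10/0.0321 − 1.96 = 1.16; probability about 12% (13% with a pooled variance). At 120 per arm it is about 26%.
- Confidence, at the primary margin in standardised form. The examination SD is not stated. Back-solving from 120 per group, margin 7, 80% power and two-sided 5% gives SD = 7/[√(2/120)·(1.96 + 0.84)] = 19.4, so the margin is 7/19.4 = 0.36 SD. At 170 per arm: 0.36/√(2/170) − 1.96 = 1.36; probability about 9%. At 120 per arm it is about 20%.

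A non-inferiority test judged by a two-sided 95% CI holds this at 2.5%.

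**4. Could margins be used at this sample size?** For 80% power at one-sided 2.5%, n per arm = (1.96 + 0.84)²·2p(1−p)/margin².

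| Pass rate | 10-point margin | 5-point margin |
|---|---|---|
| 90% | 142 | 566 |
| 95% | 75 | 299 |

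Against 170 per arm, a 10-point margin is feasible at these rates and a 5-point margin is not.

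**5. Unit-grade rationale.** 7/15 = 46.7% of the 50–65 band; 7/10 = 70% of the 50–60 band. Half of the first band is 7.5 points, so the claim of at least 50% of each band fails there.

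**The case against.** The strongest reply is that the document never says a non-significant result will be taken as non-inferiority. Logistic regression and a t test both yield estimates with confidence intervals, the raw material for a non-inferiority reading, and a margin might sit in a fuller document. The first part stands: reading non-significance as non-inferiority is something a reader might infer, because no other rule is given, but it is not stated. The last part carries less weight, since the article sets out the non-inferiority question and its analysis together without the element that would connect them. It is also fair that *similar* is a comparative question and not a declared equivalence test.

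Three stronger readings are tempting and are not supported.

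- **High false non-inferiority rates.** At 170 per arm, a true 95% v 90% pass rate is non-significant about 58% of the time, and a 0.2 SD confidence deficit about 55%. These are not error rates under the illustrative margins: 5 points lies inside a 10-point margin and 0.2 SD inside 0.36 SD, so calling them non-inferior would be correct. The relevant figures are those at the margin, about 12% and 9%.
- **The SPEF-R item rule contradicts the pass cut.** The plan says "An overall difference >1 point on the 5-point scale between groups will be considered educationally important", while "Scores of 1 or 2 indicate a failing performance", so one point separates a fail from a pass. But the rule concerns a difference between groups, not one student's step, and pass/fail is analysed separately overall and by domain. The threshold may be generous, but it breaks no criterion the document states.
- **The unit-grade threshold is unusable.** It is not. Seven is below 7.5, so the discrepancy errs on the strict side. The bands are given as examples, and the section offers a second reason: a likely shift in the allocated grade.

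**Conclusion.** The point holds for SPEF-R overall pass and for confidence: both are posed as non-inferiority questions, and the analyses named cannot support a non-inferiority conclusion without a margin and a confidence-limit rule. The learning-opportunities question has the same gap in milder form. That the mismatch exists rests on the text alone. Its size rests on assumed pass rates and margins and, for confidence, on a back-solved SD for a different outcome: roughly 9–12% non-significance at the margin with 170 per arm (20–26% with 120), against 2.5%. The primary examination outcome has its own margin and lies outside this point. The unit-grade arithmetic is a minor wording error with no analytic effect.

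**What to change.** If between-arm results are still unseen, state a margin for SPEF-R overall pass as a risk difference and a margin for confidence on the 41–205 scale, each with its reason, and conclude non-inferiority only if the 95% CI excludes a deficit as large as the margin. A claim of similar learning opportunities would need a bound on the same terms.

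If results have been seen, remove the non-inferiority and similarity wording for these outcomes and report estimates with 95% CIs only. Trial status says data collection was complete at acceptance, so which route is open must be established first.

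Separately, restate the unit-grade rationale as 47% of the 50–65 band and 70% of the 50–60 band.

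The change is to wording and reporting; no new data are needed. The cost is that fewer secondary outcomes can be called non-inferior, and a strict SPEF-R margin such as 5 points would probably not be met at this sample size even if the arms were equal at pass rates of 90–95%.
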